## Abstract

**Background:**

The use of artificial colloids is currently controversial, especially in Central Europe Several studies demonstrated a worse outcome in intensive care unit patients with the use of hydroxyethyl starch. This recently even led to a drug warning about use of hydroxyethyl starch products in patients admitted to the intensive care unit. The data on hydroxyethyl starch in non–critically ill patients are insufficient to support perioperative use.

**Methods/Design:**

We are conducting a single-center, open-label, randomized, comparative trial with two parallel patient groups to compare human albumin 5 % (test drug) with hydroxyethyl starch 6 % 130/0.4 (comparator). The primary endpoint is cystatin C ratio, calculated as the ratio of the cystatin value at day 90 after surgery relative to the preoperative value. Secondary objectives are inter alia the evaluation of the influence of human albumin and hydroxyethyl starch on further laboratory chemical and clinical parameters, glycocalyx shedding, intensive care unit and hospital stay and acute kidney injury as defined by RIFLE criteria (risk of renal dysfunction, injury to the kidney, failure of kidney function, loss of kidney function, and end-stage kidney disease) criteria.

**Discussion:**

There is a general lack of evidence on the relative safety and effects of hydroxyethyl starch compared with human albumin for volume replacement in a perioperative setting. Previously conducted studies of surgical patients in which researchers have compared different hydroxyethyl starch products included too few patients to properly evaluate clinical important outcomes such as renal function. In the present study in a high-risk patient population undergoing a major surgical intervention, we will determine if perioperative fluid replacement with human albumin 5 % will have a long-term advantage over a third-generation hydroxyethyl starch 130/0.4 on the progression of renal dysfunction until 90 days after surgery.

**Trial registration:**

EudraCT number 2010-018343-34. Registered on 11 January 2010.

## Background

Various crystalloid and colloid solutions are available to the clinician for perioperative volume replacement therapy. Colloids are large–molecular weight (nominally MW >30,000) substances. In normal plasma, the plasma proteins are the major colloids present. Albumin solutions are available for use as colloids. Various other solutions containing artificial colloids, such as hydroxyethyl starches (HESs), are commonly used in clinical praxis.

Different preparations are indicated according to the different patient types and the type of fluid loss. For some decades there have been contradicting philosophies, in particular concerning the best choice for volume substitutes to deal with perioperative blood loss. However, fluid preloading and liberal intraoperative fluid substitution are not evidence-based procedures [1]. According to current reviews, recommended rational fluid therapy includes a combination of crystalloid and colloid solutions. An adequate replacement of fluid needs seems to have the power to improve patient outcomes and should be considered the therapy of choice to minimize perioperative fluid shifting [2].

HES solutions are used for the treatment of hypovolemia (low blood volume) when plasma volume expansion is desired. There is conflicting evidence about its relative safety, most notably regarding adverse effects of HES on kidney function.

In an animal model, the application of 10 % HES 200,000 already led to a reduction of diuresis and increases in inflammation and tubular damage [3]. These effects were more distinctive in 10 % HES 200,000 than in 6 % HES 130,000 or lactated Ringer solution.

In the Efficacy of Volume Substitution and Insulin Therapy in Severe Sepsis study, conducted by the German Competence Network Sepsis, the authors compared 10 % HES 200,000 with lactated Ringer solution as volume replacement therapy in critically ill patients. In the HES group, the incidence of acute renal failure, renal replacement therapy and need for blood transfusion were significantly increased. The authors postulated that the long storage of HES molecules in the tissue and a potential direct toxicity of the substance per se could be responsible for these negative effects [4]. Indeed, these results were seen only in patients who received more than 22 ml/kg/day.

Schabinski and colleagues compared the effect of 6 % HES 130/0.4 with 4 % gelatin on renal failure and mortality in critically ill surgical patients. They showed that a significant increase in mortality and acute renal failure occurred in the HES group if the cumulative dose of 33 ml/kg body weight was exceeded [5].

A survey of 120 Scandinavian intensive care units (ICUs) published in 2008 [6] revealed that, for most physicians, colloids are a second-choice volume substitute. Only one-third were found to use it as a primary volume substitute. HES 130/0.4 was the preferred colloid. A large part of the interviewees attested that there were no internal directives or contraindications for the use of HES at their centers. At the same time, almost all interviewees indicated that they would change their infusion practice if randomized controlled studies clearly showed negative effects on mortality and renal failure [6].

An alternative to HES is the use of human albumin (HA). The safety of HA was examined in the Saline versus Albumin Fluid Evaluation (SAFE) study, published in 2004 [7]. In that large investigation, the impact of saline 0.9 % and albumin 4 % was compared in critically ill patients. Neither in the whole group nor in one of the subgroups was a relevant difference found with regard to mortality, ICU length of stay, organ failure, respiratory support or renal replacement therapy. A post hoc analysis showed that the results were independent of the serum albumin value of the patients [8]. Indeed, in a subgroup analysis, the authors found an increase in mortality in patients with brain injury who received albumin compared with those in the saline group [9]. However, this was not a negative effect of the colloid albumin, but the result of volume loading in patients who are not hypovolemic and therefore without demand of any colloid infusion [10].

In a meta-analysis, Wilkes and Navickis investigated the safety of albumin and its influence on mortality. The authors compared 55 randomized trials in patients after major surgery, trauma, burn, hypoalbuminemia, ascites and other diseases. The researchers in the included trials compared albumin therapy with crystalloid therapy, no albumin or lower doses of albumin. Overall, the authors found no effect of albumin on mortality [11].

In an experimental study, Jacob et al. [12] investigated the different negative effects of colloids on vascular permeability. The authors perfused an isolated heart (guinea pig) with 5 % albumin, 6 % HES 130/0.4 and saline 0.9 % and observed the fluid extravasation before and after 20 minutes of ischemia. This study demonstrated a significantly lower extravasation in the albumin and HES group compared with the group that was given saline 0.9 %. After ischemia, a transient increase in vascular permeability resulted from use of HES and saline 0.9 %. In the albumin group, there was no increase in vascular leakage. This effect was independent of the intravascular colloid osmotic pressure. The authors concluded that albumin interacts with the endothelial glycocalyx, which seems to be the cause of the protective effects of albumin on the vascular barrier [12].

In an investigation on isolated heart perfusion, Jacob et al. [13] examined the effects of albumin on endothelial integrity and myocardial function after 4 h of ischemia. The authors compared Bretschneider solution with and without addition of albumin. After reperfusion, intracoronary adhesion of polymorphonuclear granulocytes, edema formation, left and right heart performance of pressure-to-volume work, and glycocalyx formation were assessed. The intracoronary adhesion of leukocytes was doubled in the Bretschneider solution group, whereas it remained at basal values after albumin addition. Addition of albumin also decreased edema and led to significantly better right ventricular function. Glycocalyx shedding was significantly lower in the albumin group than in the group without albumin addition. The authors concluded that addition of albumin improves endothelial integrity as well as heart function after 4-h ischemia, owing to protection of the glycocalyx [13].

The effects of HES 200/0.6 and HES 130/0.4 on renal function after transplant were compared in a retrospective investigation by Blasco et al. in brain-dead donors [14]. Thirty-two donors were included in every group. The appearance of delayed organ function and postsurgical creatinine was documented. Delayed organ function was found in the group treated with HES 130/0.4 compared with patients treated with HES 200/0.6. The creatinine levels after 1 month amounted to 133 μmol/L in the HES 130/0.4 group and 172 μmol/L in the HES 200/0.6 group (*p* = 0.005). After 1 year, increased creatinine was found in the HES 200/0.6 group compared with the HES 130/0.4 group (147 μmol/L versus 128 μmol/L; *p* = 0.05). The authors concluded that the use of modern third-generation HES preparations are associated with better postsurgical renal function [14].

Van der Linden et al. compared HES 130/0.4 with modified 3 % gelatin solution in 132 cardiac surgery patients with regard to perioperative blood loss and transfusion need. Both groups also received a cumulative dose of 48.9 ml/kg of colloids. Blood loss, transfusion need, laboratory parameters and hemodynamics were comparable in both groups. The authors concluded that it is safe to use 50 ml/kg of HES 130/0.4 [15].

In a systematic review, Hartog and colleagues [16] identified 56 randomized controlled trials on the use of HES 130/04 in an elective surgical setting. These studies were small-sized and of short duration. The main goal was to assess whether published studies on HES 130/0.4 resuscitation are sufficiently well designed to make conclusions about the safety of this compound. The 56 studies were small, heterogeneous, and involved different control fluids and different clinical conditions. The authors concluded that the results of these studies could not be pooled and that the studies did not provide convincing evidence that third-generation HES 130/0.4 is safe in surgical, emergency, or ICU patients, despite publication of numerous clinical studies [16].

Recent data have associated the use of HES products with an increased risk of severe adverse events (SAEs) when used in certain patient populations. After a review of the available evidence [17], on 14 June 2013, the Pharmacovigilance Risk Assessment Committee of the European Medicines Agency concluded that the benefits of HES solutions no longer outweighed their risks and recommended that the marketing authorizations for these medicines be withdrawn [18]. The European Union regulatory agency then decided to restrict the indication for HES solutions. HES is now indicated only as second-line treatment after crystalloids when there is acute bleeding. The use of HES solution is contraindicated in critically ill patients, including those with sepsis, burns, transplant and cerebral bleeding, and renal impairment and/or hepatic dysfunction. On 24 June 2013, the U.S. Food and Drug Administration recommended that HES products not be used in critically ill patients or in those with preexisting renal dysfunction, but it also did not withdraw them completely.

Despite of the fact that there are several small clinical trials in which HES was compared with another fluid for volume replacement in various clinical settings, there is a general lack of evidence on the relative safety and efficacy of HES versus HA for volume replacement in the perioperative period. Previously conducted studies of surgical patients in which different HES products were compared included too few patients for proper evaluation of important clinical outcomes, such as renal function.

In the present study, we will determine, in a patient population undergoing a major surgical intervention, if perioperative fluid replacement with HA has a long-term advantage compared with a third-generation HES (HES 130/0.4) on the progression to renal dysfunction until 3 months after surgery.

### Hydroxyethyl starch 6 % 130/0.4 (Volulyte)

Blood and protein losses that occur during surgical procedures can be compensated by the patients up to a certain point. The current infusion practice is to provide a combination of crystalloid and colloid solutions. The objective is to reach hemodynamic targets and treat the diuresis of the patient to maintain sufficient organ perfusion. Guided by the hemoglobin values, blood transfusions are also used.

Protein and blood losses are currently substituted, at least in Central Europe, with HES. The common modern preparation is 6 % HES with a MW of 130 kDa and a substitution degree of 0.4 (Volulyte; Fresenius Kabi, Bad Homburg, Germany). This solution contains, in comparison with the serum value, higher sodium and chloride amounts (154 mmol/L in each case). According to the manufacturer, the maximum dose to be administered is 50 ml of hydroxyethyl starch/kg (i.e., 3500 ml for a patient of 70-kg body weight). This dose is based on experimental investigations in rats where the infusion of 9 g/kg HES showed no toxic effects. Information concerning the maximum dose to be administered in humans is absent.

Up to now, HES preparations of the modern generation were examined only in specified patient groups. No publication of a systematic investigation with information about maximum administrable dose exists in the literature. Therefore, it is unclear whether organ-toxic or coagulation-restraining effects, as proved with older HES preparations, also occur with use of the modern products.

### Human albumin 5 % (Humanalbin)

HA is a natural component of blood plasma and is responsible for colloid osmotic pressure. It has a MW of 66 kDa and acts as a transport protein for water-indissoluble substances in the blood. It binds cations as well as anions and contributes on account of these ampholytic qualities to the buffer capacity. In addition, it is an important component of the endothelial glycocalyx, which forms the so-called endothelial surface layer, together with the endothelial cell line.

HA as a colloidal volume substitute is a content of various clinical and experimental investigations. Still, there is controversial international discussion regarding this substance as infusion solution. The SAFE study investigators examined this aspect in the most recent study. Indeed, those authors compared HA with a crystalloid solution (saline 0.9 %). The safety of this substance could be proved in the whole group, even though a subgroup showed conflicting results [9].

The HA solution used in this investigation is a 5 % infusion solution (Humanalbin; CSL Behring, Marburg, Germany) with at least 96 % HA. The substance is licensed for volume replacement therapy. Dosage and infusion rate are recommended to be adjusted to the patient’s individual requirements. There is no upper dose limit.

### Trial rationale

In the present trial, data concerning postoperative renal function are the main interest, in addition to blood loss, need for transfusions and coagulation substitutes, hospital stay, and complications and mortality. Patients undergoing cystectomy will be included. These patients are considered high-risk patients for the development of progressive renal dysfunction postoperatively based on their underlying disease and the severe surgical intervention. Because of its higher accuracy, cystatin C was chosen for calculation of glomerular filtration rate (GFR) [19, 20].

Both colloid solutions, HES and HA, are used in routine clinical perioperative settings. Their comparative safety and long-term effects on renal function in perioperative patients has not been studied in well-controlled and adequately powered randomized clinical trials. It is expected that the findings of this trial will increase knowledge about fluid management in surgical patients who are at risk for developing renal dysfunction postoperatively.

### Trial objectives and endpoints

#### Primary objective

Our primary objective is to compare the effects on renal function of HA 5 % with those of HES 130/0.4 when administered for perioperative volume replacement in patients undergoing cystectomy, with the aim of demonstrating the superiority of HA over HES.

#### Primary endpoint

The primary endpoint is the cystatin C ratio, calculated as the ratio of the cystatin value at day 90 after surgery relative to the preoperative value. This ratio corresponds to the calculated GFR ratio (the value at day 90 relative to that before surgery). The calculation of the GFR is carried out with the help of cystatin C, based on the following formula:$$ \mathrm{G}\mathrm{F}\mathrm{R}\ {\left(\mathrm{ml}/ \min \right)}_{\mathrm{calculated}} = 74,835 \times \mathrm{cystatin}\ \mathrm{C}\ {\left(\mathrm{mg}/\mathrm{L}\right)}^{-1333} $$

#### Secondary objectives

Secondary objectives of the clinical investigation are the evaluation of the influence of HA and HES on further laboratory chemical and clinical parameters, ICU and hospital length of stay and acute kidney injury as defined by RIFLE criteria (risk of renal dysfunction, injury to the kidney, failure of kidney function, loss of kidney function, and end-stage kidney disease). Also, we are interested in the presence of pruritus evaluated by conducting a standardized interview.

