#### Randomization and stratification

This trial is designed as an open-label trial. Randomization will be performed at the Institute for Medical Informatics, Biometry and Epidemiology (IBE) of the University of Munich, and the treating physicians will be informed about the treatment arm to which a patient is assigned.

Randomization to both treatment arms will be performed in a ratio of 1:1. The randomization technique is based on randomized, balanced blocks with random block length. The procedure considers stratification by type of surgical procedure (ileal conduit or neobladder). The IBE will provide an internet-based randomization tool (Randoulette), which chooses the colloid treatment group for a new patient fulfilling the eligibility criteria and having signed the informed consent. Randoulette will register the patient by the patient’s pseudonym or screening number, sex, year of birth and stratum (ileal conduit or neobladder) before the allocated colloid treatment group is provided.

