### Statistical planning and analysis

#### Statistical analyses

The primary efficacy analysis statistically tests superiority of HA versus HES at an α significance level of 5 % (two-sided, simultaneously testing both sides at a level of 2.5 %) with respect to the primary endpoint.

The primary endpoint is expected to be non-normally distributed. After logarithm transformation, the primary endpoint may not be normally distributed. Thus, the corresponding statistical null hypothesis is the hypothesis that the distribution functions of the endpoint in the HA group and the HES group are equal and will be tested non-parametrically with the Mann-Whitney-Wilcoxon test to detect directed differences of the distributions. The Mann-Whitney-Wilcoxon test will be applied. The one-sided *p* value will be calculated, if possible, using Fisher’s exact test.

The primary endpoint adjusts in a specific way for the preoperative cystatin C values. At the planning stage, the Mann-Whitney-Wilcoxon test will be applied in the stratified version by type of surgical procedure (ileal conduit or neobladder). If adjustments of stratification are deemed necessary during the course of the trial, the trial protocol will be amended.

A fixed-sample design is planned. Changes of trial design, if necessary or advisable, resulting from an interim analysis without significance testing (no αspent) had to keep the prespecified significance level. In that case, the Brownian motion will be used for modeling the primary test statistic based on the accumulating data as a stochastic process (see next section).

The distributions will be described at all time points by median, minimum, maximum and quartiles separately for both the HES and HA groups.

The primary statistical analysis will be based on the intention-to-treat (ITT) principle.

Analysis of all secondary endpoints and of patient characteristics will be descriptive. Descriptive comparisons will be conducted with the *t* test or, in the case of deviations from the normal distribution, with the Mann-Whitney-Wilcoxon test, or with Fisher’s exact test in case of a binary outcome.

Safety data will be analyzed descriptively in the two groups at least every 12 months.

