#### Power considerations and sample size calculation

Three parameters will influence the sample size of the study, in which we will use the Mann-Whitney-Wilcoxon test for the statistical decision based on a fixed-sample design: the level of significance, the power of the two-sided test and the probability that an observation X_AlbuCyst_ in the HA group is less than an observation X_VoluCyst_ in the HES group. For sample size planning, no stratification and approximately normally distributed data for log-transformed cystatin C values and calculated log-transformed GFR values are assumed. The location parameter and standard deviation of cystatin C at baseline are assumed to be 0.9 mg/L and 0.2 mg/L, respectively, based on the publication by Evangelopoulos and colleagues [23]. Thereby we consider the older patient groups and greater variability because subgroups are pooled and study patients did not represent a healthy population.

For sample size calculation, the value of 0.2222 for the standard deviation of the difference at day 90 minus baseline of the log-normal transformed cystatin C values is specified in both treatment groups. There are two arguments for this specification. First, the value is suggested to be conservative in the four groups (two treatments times two measurement time points) considered in the statistical analyses. Second, adjusting for baseline values by using cystatin C values at day 90 relative to the same patients’ value at baseline is suggested to reduce rather than to increase the standard deviation.

An increase of the GFR by the factor 1.2 due to HA compared with HES would be clinically meaningful and worthwhile to be detected as statistically significant difference at a two-sided type I error level of α = 5 % with a statistical power of 1 − β = 80 %. For the interpretation of the increase of the GFR by the factor 1.2 consider, for example, a patient with a Cystatin C value of 0.9 mg/L. This value results in a calculated GFR at baseline between 86 and 87 ml/min. Then, the factor 1.2 would mean an increase of GFR at day 90 from 60 to 72 ml/min, from 65 to 78 ml/min, or from 70 to 84 ml/min.

The factor of 1.2 with respect to GFR transfers to the detectable difference of 0.1368 for the log-transformed (natural logarithm) Cystatin C values when using the conservative formula where the exponent is −1.333.

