## Appendix

**Table 1 Tab1:** Flowchart

Schedule of activities	Visit 1	Visit 2	Visit 3	Visit 4	Visit 5
	Screening day (day −1)	Day 0 (day of surgery)	Day 1	Day 3	Day 90
Informed consent	X				
Inclusion and exclusion criteria	X				
Demographic data	X				
Medical history (primary diagnosis)	X				
Pregnancy test for women of childbearing potential	X				
Mini Mental State Examination	X				
Life Quality Assessment (ADL, IADL)	X				X
Concomitant medications (diuretics)	X	X	X	X	X
Cystatin C, GFR, serum creatinine	X	X	X	X	X
ROTEM, Multiplate, PFA 100		X			
Randomization		X			
NGAL, syndecan 1, hyaluronan		X	X	X	
Study drug		X	X	X	
Blood products		X	X	X	
IV fluid amount		X	X	X	
Blood losses and urine output		X	X	X	
Nursing Delirium Screening Scale		X	X	X	
AEs and SAEs		X	X	X	X
Pruritus assessment					X

*ADL* activities of daily living, *AE* adverse event, *IADL* instrumental activities of daily living, *IV* intravenous, *NGAL* neutrophil gelatinase-associated lipocalin, *PFA 100* Platelet Function Analyzer 100, *ROTEM* rotational thrombelastometry, *SAE* serious adverse event2

**Table 2 Tab2:** Algorithm of infusions and transfusion in the operating room and intensive care unit

Hemodynamics	
ASA I and II patients without cardiac diseases or cerebral insufficiency:	
Stroke volume variation (SVV) <12 %	
Cardiac index (CI) > 2.5 L/min/m^2^	
MAD >60 mmHg	
ASA III and IV patients or patients with cardiac diseases or cerebral insufficiency:	
SVV <12 %	
CI >2.5 L/min/m^2^	
MAD >70 mmHg	
Central venous oxygen saturation >70 % or mixed venous oxygen saturation >65 %	
To reach the desired parameter:	
Start with infusion protocol (see below)	
If not successful within 15 minutes:	
Start with norepinephrine as first-choice vasopressor	
Infusion protocol	
Replacement of urine output with Ringer’s acetate solution in a 1:1 ratio	
Additionally, 500 ml of crystalloids for insensible sweating	
Replacement of blood and protein losses dependent on treatment assignment, with either HA 5 % or HES 6 % in a 1:1 ratio up to a transfusion trigger point or a maximum of 50 ml/kg/day	
Additionally up to 1500 ml of colloids for the protein loss into the third compartment

**Table 3 Tab3:** Transfusion protocol (in support of [24])

Red blood cells			
Hb (g/dl)	Risk factors	Transfusion	Evidence level
<6 g/dl	–	Yes	1c+
>6–8 g/dl	Adequate compensation, no risk factors	No	1c+
	Limited compensation or risk factors (cardiac diseases, cerebrovascular insufficiency)	Yes	1c+

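### Pruritus is asked about once, at day 90, in an open-label trial: new itch cannot be told from old, and knowledge of the arm may colour the answers

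*Protocol article*

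**What the plan says.** Under Secondary objectives the article states that "we are interested in the presence of pruritus evaluated by conducting a standardized interview". The Secondary endpoints list gives this a single time point, day 90. In Table 1 of the Appendix, the row "Pruritus assessment" has one mark, under Visit 5 (day 90). The ADL/IADL row in the same table is marked at both screening and day 90.

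Randomization and stratification says "This trial is designed as an open-label trial" and that "the treating physicians will be informed about the treatment arm to which a patient is assigned". It does not say whether patients or the day-90 interviewer are told. It also states "Randomization to both treatment arms will be performed in a ratio of 1:1", in balanced blocks stratified by type of urinary diversion.

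Statistical analyses says "Analysis of all secondary endpoints and of patient characteristics will be descriptive", with groups compared "with Fisher’s exact test in case of a binary outcome". No pruritus rate is given anywhere in the article.

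**The concern.** Pruritus is the one listed secondary endpoint that rests wholly on what the patient says. The others are laboratory values, RIFLE categories, lengths of stay and renal replacement therapy. Two features weaken it.

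- **No baseline.** A patient who itched before surgery and still itches at day 90 is recorded in the same way as one whose itch is new. New itch is the quantity a reader would want to attribute to a colloid.
- **No described masking.** If the patient or interviewer knows the colloid, expectation can affect the answer. This is plausible here. The stated aim is to show superiority of albumin, and the Background reports regulatory action against HES in June 2013, within the trial period (May 2012 to an expected February 2016).

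At stake is how far a difference in pruritus, or the lack of one, can be interpreted.

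**Working it through.** **The plan's own figure.** The article sizes only the primary endpoint, and that calculation reproduces.
- Detectable difference: ln(1.2)/1.333 = 0.1368.
- P = Φ(0.1368/(0.2222·√2)) = 0.6683.
- Noether's formula at "two-sided type I error level of α = 5 % with a statistical power of 1 − β = 80" %: N = (1.960 + 0.842)²/(3 × 0.1683²) ≈ 92.4, or 46.2 per group, rounded up to 47.
- Enrolment: 94/0.9 = 104.4, rounded up to 105.

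None of this concerns pruritus. It only supplies the 47 evaluable patients per arm used below. Every itch rate below is an assumption. Rejection rates are exact: all pairs of binomial counts are enumerated and tested with two-sided Fisher at 0.05.

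**1. Pre-existing itch with no treatment or reporting effect.** Let b be the pre-existing rate, the same in both arms in expectation because of randomisation. The expected difference is b − b = 0, with standard error √(2b(1−b)/47).

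| b | SE of difference | Fisher rejection |
|---|---|---|
| 5% | 4.5 points | 0.6% |
| 10% | 6.2 points | 1.7% |
| 20% | 8.3 points | 2.6% |

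All rejection rates are below 5%, so there is no systematic false difference. Chance imbalance is still real: at b = 10%, the arms differ by four or more itching patients about 22% of the time, and the planned data cannot show when this has happened.

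**2. Dilution of a true effect.** Suppose new itch occurs in 10% of itch-free HES patients and in none on albumin, and that pre-existing itch persists to day 90. The HES arm then shows b + (1−b) × 0.10 and the albumin arm shows b. The observed difference is (1−b) × 0.10.

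| b | Observed difference | Fisher power |
|---|---|---|
| 0% | 10.0 points | 33% |
| 5% | 9.5 points | 20% |
| 10% | 9.0 points | 14% |
| 20% | 8.0 points | 10% |

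With a baseline question and b = 10%, about 47 × 0.9 ≈ 42 patients per arm are itch-free at baseline. Comparing 0% with 10% among 42 per arm gives about 24% power, against 14% as planned. Fisher's test is coarse at such small counts, so these powers are indicative. The gain comes from removing background itch.

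**3. Reporting shift with no true effect.** The true rate is 10% in both arms and only the reported HES rate rises.

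| Reported HES rate | Fisher p<0.05 |
|---|---|
| 10% (no shift) | 1.7% |
| 14.5% | 4.8% |
| 20% | 17.6% |
| 25% | 37.5% |
| 30% | 59.9% |

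The 14.5% row corresponds to 5% of otherwise itch-free HES patients over-reporting: 0.10 + 0.90 × 0.05 = 0.145. A small shift therefore does little harm, and a large one would dominate the comparison.

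**The case against.** The strongest reply is that nothing confirmatory depends on pruritus. It is one of seven secondary endpoints, all analysed descriptively, and the primary endpoint is a laboratory ratio that self-report cannot alter. Counting p<0.05 as an error treats a descriptive comparison as a decision rule. This stands and limits the weight of the point, although the comparison will still be tested and reported.

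A second reply is that the article condenses a fuller protocol, which may describe the interview form, any question on onset and who conducts the interview. This stands for masking of the interviewer. It is weaker for the baseline, because the endpoint list and Table 1 both positively fix a single day-90 assessment while ADL/IADL is given two. Screening does record medical history, but Table 1 ties it to the primary diagnosis. Adverse events are recorded only from day 0. Neither is described as a baseline question about itch.

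A reader might infer that pre-existing itch is counted as a treatment effect. It is not: with 1:1 randomisation its expected difference is zero. A reader might also infer that expectation about HES does distort the result. The article does not say what patients are told about HES and itch, or whether the interviewer knows the arm, so the bias is possible but not shown.

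Finally, one might want the allocation withheld from patients until after day 90. That would change a deliberately open-label design. The article does not say that most of the colloid is given under anaesthesia, and it describes colloid use continuing after surgery, so how far patients could be masked is unknown.

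**Conclusion.** The point holds as a minor one. The single day-90 question in an open-label trial means that new and pre-existing itch cannot be separated, that a true difference is diluted by (1 − baseline rate), and that chance imbalance cannot be checked. At an assumed 10% baseline rate, a true 10-point excess shows as 9 points, and power falls from 33% to 14%. Reporting bias from knowledge of the arm is an additional possibility whose size cannot be estimated from the document: the chance of p<0.05 ranges from about 5% to about 60% over the shifts assumed.

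These figures rest on assumed itch rates, persistence of baseline itch to day 90, and 47 evaluable patients per arm. They do not show that any pruritus result from this trial is wrong, and they have no bearing on the primary analysis.

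**What to change.** 1. In Table 1, add a mark for the pruritus assessment at Visit 1, beside ADL/IADL.
2. Report pruritus at day 90 that was absent at baseline, alongside overall presence at day 90. For patients already enrolled without a baseline answer, report overall presence only.
3. At Visit 5, complete the standardised pruritus questions before the allocation or infusion record is opened.

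The cost is one extra question at screening and a short instruction for Visit 5. The limits are that patients already past screening cannot supply a baseline, and that masking will be incomplete because some patients or staff will know the arm anyway. The third step can still be applied to every day-90 visit not yet held.
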